**Prescriber Report Metrics**		
**RRT Initiation Criteria**		**Benchmarks**^**a**^
Serum potassium		> 6.0 mmol/L
pH		< 7.20
Serum bicarbonate		< 12 mmol/L
Oxygenation status		Impaired oxygenation as per P/F ratio of < 200
Cumulative volume status		Cumulative Fluid Balance defined as > 10% positive fluid balance^b^ anchored from time of ICU admission

^a^Benchmarks obtained from STARRT-AKI inclusion criteria

^b^Cumulative Fluid Balance is calculated as (fluid intake – fluid output in liters since ICU admission) / (weight in kilograms) × 100%

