#### Prescriber reporting

An ICU-specific prescriber and program report will be provided to each prescriber and ICU on a quarterly basis. The report will include: 1) the number of acute KRT initiations, 2) acute KRT initiations based on conventional indications (i.e., hyperkalemia, acidosis, metabolic status, oxygenation status and cumulative fluid status) termed ‘appropriate initiations’, 3) general guidelines of KRT initiation criteria as per STARRT-AKI standard initiation arm protocol. (Table 2) [5] These will be benchmarked against prescriber patterns from providers in the same ICU, as well as similar ICUs across Alberta.

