APACHE II Score	number
SOFA score	number
Invasive/non-invasive ventilation	hrs/min
Vasopressors (include type)	hrs/min
CRRT/IHD/SLED	hrs/min
Cumulative daily fluid balance prior to RRT	mls
Creatinine, urea, pH, bicarbonate, potassium on day of RRT initiation	result
Renal Recovery at ICU Discharge	y/n - IHD
Renal Recovery at Hospital Discharge	y/n – IHD/PD
Renal Recovery at 6 Months	y/n - IHD/PD
ICU Mortality	A/D
Hospital Mortality	A/D
6-month Mortality	A/D
ICU length of Stay	days
Hospital Length of Stay	days
Number of admissions to site	aggregate
Patient days	aggregate
Ventilator days	aggregate
RRT days	Days CRRT/IHD/SLED
CRRT and IRRT data - filter life, reasons for retiring filters, treatment time lost, prescription/dose, machine alarms, machine down times, type of coagulation, blood flow rates, filtration fraction, adverse events, solute clearance, ultrafiltration realized	aggregate
Economic data - cost of filters, fluids, anticoagulation medications, RRT catheters, patient life-years gained, quality of life adjusted years (QUALY), re-hospitalizations, recurrence/chronic RRT, health care provider related costs	aggregate
QOL and PROMs	aggregate

Data sources will include multiple Alberta Health Services administrative databases, the Nephrology Information System (NIS) and the Patient Based Renal Information System (PARIS) (Supplementary Table 1) [20, 21].

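### Table 4 does not match the outcomes it should supply: no P/F ratio, laboratory values tied only to the day of KRT start, and no day-90 status

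*Protocol article*

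**What the plan says.** **Appropriate initiation.** The section Primary outcomes of the protocol article includes the number of appropriate KRT initiations. Prescriber reporting defines these by conventional indications: "hyperkalemia, acidosis, metabolic status, oxygenation status and cumulative fluid status". The Prescriber Report Metrics in Table 2 give five benchmarks: potassium, pH, bicarbonate, oxygenation ("Impaired oxygenation as per P/F ratio of < 200") and fluid ("Cumulative Fluid Balance defined as > 10% positive fluid balance", counted from ICU admission).

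**What is captured.** Data management introduces Table 4 as a summary of the variables to be captured. Those relevant to initiation are "Creatinine, urea, pH, bicarbonate, potassium on day of RRT initiation", "Cumulative daily fluid balance prior to RRT", weight, ventilation time, and APACHE II and SOFA as single numbers.

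**Follow-up outcomes.** Secondary outcomes include mortality at 90 days and KRT dependence at 90 days. Table 4 records mortality in ICU, in hospital and as "6-month Mortality". It records renal recovery at ICU discharge, at hospital discharge and as "Renal Recovery at 6 Months".

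**Sources.** The data come from several administrative databases and two renal information systems, detailed in a supplementary table that is not shown.

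**The concern.** An extract built from Table 4 as written would lack one input to a primary outcome, would leave the timing of three others open, and would hold follow-up at time points other than those of two secondary outcomes.

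The initiation classification has two uses. It is analysed before and after implementation. It also goes back each quarter to individual prescribers, and under Stakeholder education the study team contacts selected outliers. A misclassified start therefore affects feedback to clinicians as well as the estimate.

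Timing matters because KRT itself corrects potassium and acidosis. A value drawn on the same day but after the start can look normal although the indication was present. Roll-out coincides with site activation of the new clinical information system. If older and newer sources return different same-day values, that difference would coincide with the intervention. The article does not say how baseline values are selected, so this is a risk and not a demonstrated fault.

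For follow-up, the section on time of KRT initiation rests its rationale on a trial result for maintenance KRT at 90 days. Reporting 6 months in its place would lose that comparability.

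**Working it through.** The plan gives no figure to reproduce here, so the check sets each outcome component beside the variable listed for it.

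**1. Initiation criteria (Table 2 against Table 4)**

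| Criterion | Variable in Table 4 | Timing stated |
|---|---|---|
| Potassium | yes | day of initiation |
| pH | yes | day of initiation |
| Bicarbonate | yes | day of initiation |
| Oxygenation (P/F) | none | not applicable |
| Cumulative fluid balance | yes, with weight for the formula | before KRT |

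Four of five criteria have a variable and one has none. Of the four, one is timed before KRT and three only to the day.

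SOFA does not fill the gap. It is listed as one number, and the same total can arise from different organ contributions, so it does not show whether the P/F ratio was below 200. Ventilation time carries no gas-exchange value.

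**2. Effect of omitting the P/F criterion, if it were omitted**

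Let *p* be the true proportion of appropriate starts and *q* the share of all starts that meet the oxygenation criterion only. Without a P/F ratio the observed proportion is *p* − *q*. With subscript 0 for baseline and 1 for intervention:

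(*p*1 − *q*1) − (*p*0 − *q*0) = (*p*1 − *p*0) − (*q*1 − *q*0)

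- The level within each period is too low by *q*.
- The before-after change is biased only by the change in *q*. If *q* is constant, this bias cancels from the change, though not from the prescriber reports.
- *q* may not be constant, because the intervention acts on the reasons for starting KRT.

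The documents give neither *q* nor its change, so no number can be put on this.

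**3. Follow-up time points (Secondary outcomes against Table 4)**

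None of the three mortality time points is day 90, and none of the three renal time points is. Assuming that the 90-day and 6-month clocks start at about the same event, the listed items give the following.

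*Vital status at day 90*
- Alive at 6 months: alive at day 90.
- Died in hospital: the death can be dated from admission date plus length of stay.
- Died after discharge but before 6 months: cannot be placed before or after day 90, unless the hospital stay had itself reached day 90. No date of death is listed.

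*KRT dependence at day 90*
- Dialysis status differs between hospital discharge and 6 months: the change may fall on either side of day 90.
- Status is the same at both points: day-90 status is likely the same, but this is inferred and not observed.
- Died between discharge and 6 months: there is no 6-month renal status, and day-90 status is unknown.

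So 90-day mortality is derivable except in essentially one group, while day-90 KRT dependence is not derivable in general.

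**The case against.** The strongest reply is that Table 4 is a summary in a journal article. The databases behind it may well hold blood gases, death dates and dated dialysis sessions, and the supplementary table on sources is not shown. Some listed items presuppose dates: fluid balance before KRT needs a KRT start time, life-years gained need survival time, and quarterly review of new dialysis intake needs dated records. A rule such as the last value before start is ordinary extraction detail. The definition itself counts oxygenation as an indication, so the simplest explanation is a line left out of the table.

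Much of this stands. It rules out several stronger readings that a reader might infer:

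- *The captured data cannot yield the outcomes at all.* Not supported. Four of five criteria have a variable, 90-day mortality is mostly derivable, and the linked sources may supply the rest.
- *No criterion is timed before the start.* Wrong for fluid balance.
- *Starts justified by oxygenation alone will be scored inappropriate.* The text does not say so. It would follow only if the classification were run on the variables in Table 4 alone.
- *The yearly number of misclassified starts can be estimated.* The 2019 figure of 1278 counts patients, not starts. It refers to 18 adult ICUs, while the evaluation covers 15 adult and 3 pediatric units. Nothing in the documents splits starts by indication.

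The reply does not remove the conflict. This is not only missing detail. The article prints a variable list with explicit timings, and those timings disagree with its own outcomes: 6 months against 90 days, and day of initiation for the laboratory values against before KRT for fluid. Availability in a source makes correction easy, but it does not make the sections agree.

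**Conclusion.** The point holds as a mismatch between the outcome definitions and the variable list. One of the five criteria behind a primary outcome has no listed variable. Three of the other four have timing that admits values taken after treatment began. Neither 90-day secondary outcome has a day-90 item, and of the two only mortality can largely be recovered from what is listed.

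This rests on reading Table 4 as the specification of the extract. If the supplementary table or a data dictionary already contains the P/F ratio, a pre-start rule and the dates, only the printed table needs correcting. The size of any bias in the initiation outcome is unknown. The point should be settled before data extraction and before the first prescriber reports, but it does not undermine the design.

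**What to change.** 1. Add the P/F ratio to Table 4.
2. Define the P/F ratio, potassium, pH and bicarbonate as the last value before the date and time of KRT start. Apply the same rule in the baseline and intervention periods, whichever information system supplies the value.
3. Add vital status and dialysis status at day 90, or dates of death and of KRT sessions from the linked databases so that both can be derived. The alternative is to change the outcome time point to one that Table 4 captures. Either way, Secondary outcomes and Table 4 must agree. The 6-month items can stay as an additional time point.

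The cost is a few extra fields in an electronic extract, with no patient contact. Moving the outcome to 6 months would need no new follow-up items, but it would lose comparability with the 90-day result that motivates the programme.

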### Co-enrollment

Co-enrollment into other clinical research studies will be evaluated on a case-by-case basis.

### Statistical analyses

#### Health outcome measures

The patients’ characteristics and the target clinic outcomes in the baseline and intervention periods will be summarized. Mean (SD) and/or median (IQR) will be used for continuous variable; frequency will be used for categorical variables. To compare pre- and post-intervention difference, *p*-values will be provided by t-test (for normally distributed variables), non-parametric Wilcoxon tests (for non-normally distributed variables) or Chi-square test (for categorical variables). Interrupted time series (ITS) analyses will use autoregressive integrated moving average (ARIMA) models to determine changes in the KPI performance following the implementation of the acute KRT pathway.

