## Background

Acute kidney replacement therapy (KRT) is a core life support technology used in approximately 10–12% of critically ill patients [1]. It is generally used to support patients with overt kidney failure or as part of a broader strategy for multi-organ support in ICU settings, along with mechanical ventilation and vasoactive medications. Its utilization has expanded, with recent estimates showing growth of more than 10% per year [2, 3]. Acute KRT in the ICU can be delivered intermittently (i.e., intermittent kidney replacement therapy [IKRT]) or continuously (i.e., continuous kidney replacement therapy [CKRT]) depending on the available technology.

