### Acute KRT in Alberta

In 2019, acute KRT was initiated in 1278 patients across 18 adult ICUs in Alberta, which represents 5–8% of our critically ill population. This coincides with 3278 KRT patient-days of continuous KRT and 398 intermittent KRT patient-days with estimated direct healthcare costs of $764–865 per day and $528 per day, respectively [3, 4]. Non-adherence to evidence-based practice may have led to an additional 56 patients per year with new end stage kidney disease (ESKD) [5]. These survivors of critical illness complicated by severe AKI, who are now receiving maintenance dialysis after hospital discharge, have attributable healthcare costs exceeding $100,000 annually per patient [6, 7]. These costs do not include associated travel and lost work time costs as well as significant impairments in the quality of lives of these patients. Strategies are needed to standardize and reduce variations in care, improve patient centered outcomes, improve health system efficiencies and reduce patient and health care system costs.

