## Methods/design

Dialyzing Wisely is a multi-centre, registry embedded, stepped-wedged, interrupted time-series evaluation of the implementation of an evidence-based and best practice acute KRT pathway in the 15 adult general and cardiac ICUs and 3 pediatric general and cardiac ICUs in Alberta that provide acute KRT (Table 1). This implementation plan will follow the principles of the Learning Health System Knowledge to Action Framework (Fig. 2) [16].

**Table 1 Tab1:** Alberta ICUs Delivering KRT

Site	City/Zone^**a**^	ICU Type	Hospital Type	Beds
University of Alberta Hospital General Systems ICU	Edmonton	Mixed	Academic	32
Mazankowski Alberta Heart Institute Cardiovascular ICU	Edmonton	Cardiac surgery	Academic	24
Mazankowski Alberta Heart Institute Cardiac ICU	Edmonton	Cardiac	Academic	8
Royal Alexandra Hospital ICU	Edmonton	Mixed	Academic	25
Grey Nuns Hospital ICU	Edmonton	Mixed	Community	8
Misericordia Hospital	Edmonton	Mixed	Community	10
Sturgeon Hospital ICU	Edmonton	Mixed	Community	5
Stollery Children’s Hospital Pediatric ICU	Edmonton	Mixed	Academic	16
Stollery Children’s Hospital Pediatric Cardiac ICU	Edmonton	Cardiac	Academic	16
Foothills Medical Centre ICU	Calgary	Mixed	Academic	28
Foothills Medical Centre Cardiovascular ICU	Calgary	Cardiac surgery	Academic	16
Foothills Medical Centre Cardiac ICU	Calgary	Cardiac	Academic	18
Peter Lougheed Centre ICU	Calgary	Mixed	Academic	18
Rockyview General Hospital ICU	Calgary	Mixed	Community	10
South Health Campus ICU	Calgary	Mixed	Community	10
Alberta Children’s Hospital Pediatric ICU/PCICU	Calgary	Mixed	Academic	15
Red Deer Regional Hospital ICU	Red Deer/Central	Mixed	Regional	12
Chinook Regional Hospital ICU	Lethbridge/South	Mixed	Regional	7

Edmonton zone provides acute KRT to North Zone patients as there are no KRT programs currently operating in North Zone ICU

^a^Alberta Health Service (AHS) is organized into five geographic zones: North (pop. 480,924), Edmonton (pop. 1,422,009), Central (pop. 476,6774), Calgary (pop. 1,710,560) and South (pop. 311,514) https://www.albertahealthservices.ca/assets/about/publications/ahs-ar-2020/zones.html

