### Interventions, duration and frequency of follow-up

The acute KRT pathway will consist of two specific interventions:Monitoring, reporting and audit of acute KRT KPIs.Provision of individualized prescriber and program reports for acute KRT initiation patterns.

The acute KRT care pathway will be implemented in a stepwise fashion with a pilot followed by randomized stepped wedge roll out at centres across Alberta over the subsequent 21 months. Roll out of ICUs will be performed in clusters and will coincide with individual site activation of a novel, province-wide electronic provincial clinical information system (CIS), Connect Care (EPIC, Verona WI).

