#### KPI and interrupted time series analysis

Interrupted time series (ITS) analyses will be done using autoregressive integrated moving average (ARIMA) models to account for temporal trends and to determine whether there were changes in the process and clinical outcomes at the intervention period (compared with the baseline period) associated with implementation of the evidence-based acute KRT pathway. Each KPI will be assessed separately, as well as in aggregate with other KPIs. Autocorrelation, partial autocorrelation, and inverse autocorrelation functions will be assessed for model parameter appropriateness and seasonality. Stationarity will be assessed using the autocorrelation function and the augmented Dickey–Fuller test. The presence of ‘white noise’ was assessed by examining the autocorrelations at various lags, using the Ljung–Box χ2 statistic.

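### The named pre/post tests (t, Wilcoxon, chi-square) ignore ICU clustering and calendar time, so their p-values are not valid in a randomised stepped wedge of 18 ICUs

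*Protocol article*

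**What the plan says.** **Design.** Under Methods/design the study is introduced thus: "Dialyzing Wisely is a multi-centre, registry embedded, stepped-wedged, interrupted time-series evaluation". It covers 15 adult and 3 paediatric ICUs. Under Interventions, duration and frequency of follow-up, implementation is "a pilot followed by randomized stepped wedge roll out at centres across Alberta over the subsequent 21 months", and "Roll out of ICUs will be performed in clusters and will coincide with individual site activation" of the new clinical information system.

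**Pre/post tests.** Under Statistical analyses, Health outcome measures, patient characteristics and target outcomes are summarised for the baseline and intervention periods. The p-values for the difference "will be provided by t-test (for normally distributed variables), non-parametric Wilcoxon tests (for non-normally distributed variables) or Chi-square test (for categorical variables".

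**Time series.** Under KPI and interrupted time series analysis, the analyses "will be done using autoregressive integrated moving average (ARIMA) models to account for temporal trends" and to detect changes in process and clinical outcomes between the two periods. Seasonality and stationarity are to be checked. The section does not say whether a series is built per ICU or for the province, or how different start dates enter.

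**Cluster term.** The only model with one is the linear mixed model for patient-reported outcome scores, which has a random intercept for cluster.

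**The concern.** In a stepped wedge every ICU moves from unexposed to exposed, so exposed observations come on average from later calendar time. A two-sample test that pools all pre and all post observations has two faults here:

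- **Bias.** A change over time that has nothing to do with the pathway enters the pre/post difference in full.
- **Wrong variance.** ICUs that switch early contribute mostly post data, and late ones mostly pre data. Stable differences between ICUs therefore leak into the contrast, while the test treats all observations as independent.

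The units in Table 1 range from 5 to 32 beds and mix cardiac, general, paediatric, academic and community settings, so some between-ICU variation is to be expected. At stake are the p-values for the target outcomes, such as appropriate initiations, entry to maintenance KRT, mortality and lengths of stay. The tests are named, so this is a stated method that does not match the design, not detail left to a fuller document.

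**Working it through.** The article gives no sample size, ICC or effect size, so there is no planned figure to reproduce. The check is the false-positive rate when the pathway does nothing.

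**From the document.** 18 ICUs; 1278 patients in 2019, spread by the Table 1 beds (278 in all), which after rounding gives 318 per quarter; 21 months of roll-out = 7 quarters.

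**Assumed.** One baseline quarter (8 quarters in all); 6 steps of 3 ICUs; continuous outcome with SD 1; ICC 0 to 0.10; cluster autocorrelation 1.0 or 0.8; linear drift of 0, 0.02 or 0.05 SD per quarter; two-sided 5% level.

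**Step 1: bias, by hand (equal-sized ICUs).** Number the quarters 0 to 7, with an ICU in step s (1 to 6) switching at quarter s.
- Mean pre time = 35/21 = 1.67 quarters.
- Mean post time = 133/27 = 4.93 quarters.
- Gap = 3.26 quarters.
- False effect = drift × gap: 0.02 × 3.26 = 0.065 SD; 0.05 × 3.26 = 0.163 SD.

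**Step 2: variance, by hand (equal-sized ICUs, autocorrelation 1.0, no drift).** There are 81 post and 63 pre ICU-quarters, and 318 × 8 = 2544 patients, so n1 = 1431 and n0 = 1113.
- The t-test assumes variance h = 1/1431 + 1/1113 = 0.001597.
- The true variance is (1 − ICC) × h + ICC × S, where S is the sum over ICUs of ((8 − s)/81 − s/63)². This gives S = 0.0418.
- The rejection rate is the two-sided normal tail beyond 1.96/√(true variance/h).

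| ICC | true variance | ratio to h | rejection by hand |
|---|---|---|---|
| 0 | 0.00160 | 1.00 | 5.0% |
| 0.01 | 0.00200 | 1.25 | 8.0% |
| 0.05 | 0.00361 | 2.26 | 19.2% |
| 0.10 | 0.00562 | 3.52 | 29.6% |

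**Step 3: simulation with bed-weighted volumes (1500 runs per setting).** Ranges cover the settings run.

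| drift per quarter | ICC | pooled t-test rejects | mean false effect |
|---|---|---|---|
| 0 | 0 | 5.7% | 0 |
| 0 | 0.01 | 7.5-8.4% | about 0 |
| 0 | 0.05 | 20.7-21.5% | about 0 |
| 0 | 0.10 | 31.3-34.2% | about 0 |
| 0.02 SD | 0 to 0.10 | 36-48% | about 0.065 SD |
| 0.05 SD | 0 to 0.10 | 86-99% | about 0.16 SD |

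Hand and simulated results agree; at ICC 0.05 and 0.10 the simulated rates are slightly higher, as unequal ICU sizes would produce. A regression with ICU effects, quarter effects and ICU-robust standard errors, fitted to the same data, rejected 3.3-5.2% in every setting, with bias of at most 0.006 SD.

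**Step 4: ARIMA with one common interruption date.** This was a single pooled monthly series (12 baseline + 21 roll-out months, ICC 0.05, no drift), fitted with AR(1) errors, a linear trend and one step at the first start date; 150 runs, some with convergence warnings. With no effect it rejected 6.0%, so there is no clear inflation. With a true effect of 0.3 SD the mean estimate was −0.01 and it rejected 7.3%. At the first start date only 3 of 18 ICUs are exposed; the later gradual rise is absorbed by the trend term.

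**The case against.** The strongest defence is that the pre/post tests sit in a descriptive paragraph and are nowhere called confirmatory, while ARIMA carries the inference for KPIs and for process and clinical outcomes. This limits the damage but does not remove it: the paragraph still promises p-values for the pre/post difference in outcomes.

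The size of the error also depends on assumptions. That stands: at ICC 0.01 without drift the inflation is small, and with neither there is practically none.

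Four stronger readings are tempting but are not supported:

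- **That ARIMA also reads trend as effect.** It is specified to deal with temporal trends, and the check showed no clear inflation. Nor does the article say that the series are pooled. One series per ICU with its own start date would respect the staggering.
- **That ICU-level series are too sparse.** The article's 2019 totals, "3278 KRT patient-days of continuous KRT and 398 intermittent KRT patient-days", give 3278/18/4 = 45.5 and 398/18/4 = 5.5 days per ICU-quarter. That is an equal split over very unequal units, and neither the time unit of the series nor the baseline length is stated.
- **That outcome drift is documented.** The Background's "recent estimates showing growth of more than 10% per year" concerns KRT utilisation, not mortality, length of stay or KPI attainment. Drift is a risk, not a reported fact.
- **That only aggregate KPI data are held.** Table 4 puts the same aggregate label on quality-of-life and patient-reported measures, yet the latter are analysed as scores with a baseline covariate.

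**Conclusion.** The point holds for the pre/post p-values. In this design they are not protected against ICU clustering or secular trend. Under the stated assumptions the nominal 5% becomes about 8% to 34% for ICC 0.01 to 0.10 without drift, and 36-48% with a drift of 0.02 SD per quarter. ICC, drift, baseline length and step layout are all assumed, and the rates were computed for the t-test on a continuous outcome. The Wilcoxon and chi-square tests share the structural fault, but their exact rates would differ.

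For ARIMA the conclusion is narrower. The series level and start-date handling are not stated. A single pooled series with one interruption date would be a poor fit and could miss a real effect. ARIMA on its own also leaves unused the concurrent comparison with ICUs that have not yet switched, which the randomised roll-out provides.

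**What to change.** 1. Keep the pre/post tables as description and drop their p-values.
2. For KPIs, appropriate initiations, entry to maintenance KRT, mortality, lengths of stay and KRT duration, base inference on a mixed model or GEE. Include ICU effects, calendar-period effects and a time-varying pathway indicator that switches on at each ICU's own start, with a small-sample correction for 18 ICUs (for example Kenward-Roger in a linear mixed model).
3. Retain ARIMA as a complementary analysis: one series per ICU aligned to its own start, with estimates combined across ICUs, not one common interruption date.
4. Leave the cost analysis to its own plan. The patient-reported outcome model already has a cluster term.

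**Cost.** Revised wording and some programming; the planned SAS software can fit these models. Intervals will be wider. One limit remains: each ICU's start coincides with activation of the information system, so this model cannot separate the pathway's effect from that change, and the report should say so.
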